#### 4.8.5 Pre-specified subgroup analysis

No formal subgroup comparative analysis is planned for the primary or secondary outcomes. However, the effect of the intervention on the primary outcome within subgroups, will be presented using forest plots to visually examine whether it differs according to some variables, such as: (1) Journals that actively implement the CONSORT Statement (defined as requiring authors to submit a completed CONSORT checklist alongside their manuscript) vs. journals that are not actively implementing the CONSORT Statement; (2) sample size ( $n < 100$  vs.  $n \geq 100$ ); and (3) impact factor ( $<5$ ,  $5.1-10$ ;  $>10$ ) as there is evidence that higher impact factor as well as higher sample size are associated with higher adherence to reporting guidelines (44). These analyses will be exploratory, with the aim of supporting new hypothesis generation, rather than conclusive.

## **5 Legal and general logistics**

### **5.1. Organisation of study**

#### 5.1.1 Coordinating centre

The coordinating centre's, will be the Centre for Statistics in Medicine at the University of Oxford under the responsibilities of [name] and [name].

The coordinating centre's will ensure the following missions:

- Training of the staff
- Implementation of quality control
- Logical controls of data
- Follow-up on requests for correction/validation
- Statistical analysis
- Archiving of data

## 5.2. Regulatory aspects

Ethical approval for this study will be sought from the Central University Research Ethics Committee (CUREC) of the University of Oxford. Any amendments in the conduct of the study, collection of outcomes or analysis will be reported to the CUREC. The tested intervention has the goal to improve the quality of published journals (i.e. the adherence to CONSORT) and could also be implemented as usual practice without testing at the journal level. In agreement with another study, testing a similar intervention (45), we think that it is ethical to conduct this study without obtaining written consent. The main reason for this procedure are the following:

- Informing the authors and peer-reviewers would make it impossible to measure the effect of our intervention. In short, informing peer-reviewers and authors would create an artificial context which would not be comparable any more to the “real world context”. Authors and peer-reviewers would most likely be much more aware of CONSORT if they received information about the study. Furthermore, being aware to participate in a study could strongly influence the natural behaviour of peer-reviewers (e.g. putting more effort into reviewing a manuscript than under “real world conditions”) but also of authors.
- The intervention does not pose any risk of harms for authors and peer-reviewers.
- The intervention is not a medical intervention but rather tries to improve the research quality and journal processes.
- Several journal series (e.g. BMJ series) have Company Privacy Statements in place which clearly mention that research programmes might be in place for quality improvement.
- The intervention could be part of the routine at any Journal without previous assessment of its efficacy.

- No data which identifies participating manuscripts will be published.

## **6 Publication policy and access to data**

The results from this study will be published in a peer-reviewed journal irrespective of the study results. Authorship to publications will be granted according to the rules of the International Committee of Medical Journal Editors (ICMJE). We plan to publish the full anonymised dataset as a supplementary file together with the main publication.

## Appendix

Appendix 1: Example of the email which will be sent out in the intervention arm (C-Short).  
The exact wording might be slightly adapted according to the journal preferences.

Dear *\*Title, Name\**,

We thank you for accepting to peer-review a manuscript for *\*journal name\**. As we are trying to improve the reporting for randomised controlled trials according to the CONSORT guidelines, we would like to ask if you could check whether the following most important and poorly reported items are adequately implemented as indicated in the *table below/attached table*.

| Item | Section                         | CONSORT item                                                                                                                                                                            | Short explanation                                                                                                                                                                                                                                                                                                                        |
|------|---------------------------------|-----------------------------------------------------------------------------------------------------------------------------------------------------------------------------------------|------------------------------------------------------------------------------------------------------------------------------------------------------------------------------------------------------------------------------------------------------------------------------------------------------------------------------------------|
| 1    | Outcomes (6a)                   | Completely defined pre-specified primary outcome measure, including how and when they were assessed                                                                                     | Is it clear (1) what the primary outcome is (usually the one used in the sample size calculation), (2) how it was measured (if relevant; e.g. which score used), (3) at what time point, and (4) what the analysis metric was (e.g. change from baseline, final value)?                                                                  |
| 2    | Sample size (7a)                | How sample size was determined                                                                                                                                                          | Is there a clear description of how the sample size was determined, including (1) the estimated outcomes in each group; (2) the $\alpha$ (type I) error level; (3) the statistical power (or the $\beta$ (type II) error level); and (4) for continuous outcomes, the standard deviation of the measurements?                            |
| 3    | Sequence generation (8a)        | Method used to generate random allocation sequence                                                                                                                                      | Does the description make it clear if the "assigned intervention is determined by a chance process and cannot be predicted"?                                                                                                                                                                                                             |
| 4    | Allocation concealment (9)      | Mechanism used to implement random allocation sequence (such as sequentially numbered containers), describing any steps taken to conceal the sequence until interventions were assigned | Is it clear how the care provider enrolling participants was made ignorant of the next assignment in the sequence (different from blinding)? Possible methods can rely on centralised or "third-party" assignment (i.e., use of a central telephone randomisation system, automated assignment system, sealed containers).               |
| 5    | Blinding (11a)                  | If done, who was blinded after assignment to interventions (for example, participants, care providers, those assessing outcomes)                                                        | Is it clear if (1) healthcare providers, (2) patients, and (3) outcome assessors are blinded to the intervention? General terms such as "double-blind" without further specifications should be avoided.                                                                                                                                 |
| 6    | Outcomes and estimation (17a/b) | For the primary outcome, results for each group, and the estimated effect size and its precision (such as 95% confidence intervals)                                                     | Is the estimated effect size and its precision (such as standard deviation or 95% confidence intervals) for each treatment arm reported? When the primary outcome is binary, both the relative effect (risk ratio, relative risk) or odds ratio) and the absolute effect (risk difference) should be reported with confidence intervals. |
| 7    | Harms (19)                      | All-important harms or unintended effects in each group                                                                                                                                 | Is the number of affected persons in each group, the severity grade (if relevant) and the absolute risk (e.g. frequency of incidence) reported? Are the number of serious, life threatening events and deaths reported? If no adverse event occurred this should be clearly stated.                                                      |
| 8    | Registration (23)               | Registration number and name of trial registry                                                                                                                                          | Is the registry and the registration number reported? If the trial was not registered, it should be explained why.                                                                                                                                                                                                                       |
| 9    | Protocol (24)                   | Where trial protocol can be accessed                                                                                                                                                    | Is it stated where the trial protocol can be assessed (e.g. published, supplementary file, repository, directly from author, confidential and therefore not available)?                                                                                                                                                                  |
| 10   | Funding (25)                    | Sources of funding and other support (such as supply of drugs) and role of funders                                                                                                      | Are (1) the funding sources, and (2) the role of funder(s) described?                                                                                                                                                                                                                                                                    |

Your efforts are highly appreciated.

Kind regards,

*\*journal name\**-Team

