## 4. Methods

### 4.1 Trial design

This study is a multicentre RCT with articles being the unit of randomisation (Figure 1; allocation ratio 1:1). A multicentre parallel arm RCT with randomisation at the individual article level was chosen instead of a cluster RCT because the risk of any “contamination” on journal level is not given as the intervention will be implemented by an external researcher (i.e. BS). The possibility of contamination due to the possibility that peer reviewer are invited to assess several RCTs and are randomised into both arms was judged as relatively small and therefore we do not plan to adjust for clustering by journal. The journal staff (i.e. editors) will not be actively told which manuscript was allocated to the proposed intervention and which to the control group.

**Figure 1:** Study flowchart

[figure not shown]

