#### 4.3 Interventions

#### Experimental group: C-short plus usual practice

After accepting to review an article, peer reviewers will receive the automated, journal specific standard email with general information as per each journal's usual practice (e.g. where to access the manuscript, date when the peer review report is due). In addition, peer-reviewers who received a manuscript which was randomised to C-short will receive an additional email including a short version of the CONSORT checklist (C-short) (either within the email or as an attachment; based on the preferences and possibilities of the journal) focusing on the 10 most important and most poorly reported items (Table 1; as previously defined by a group of experts of the CONSORT Group (38)). Peer-reviewers will be asked to pay particular attention to items in the C-short checklist and request authors to report on these items, if not already adequately reported. This second email, containing the C-short checklist, is not generated automatically within the existing journal editorial management system (e.g. ScholarOne or Editorial Manager); it will be sent by the investigator who has access to the journal editorial system (BS). An example of this additional email is presented within the appendix (appendix 1; the exact wording might be changed according to the preferences of the participating journals). At least twice a week the editorial management system will be checked for each journal and if a peer reviewer has accepted an invitation to review, an email containing the C-short intervention will be generated and sent. It might be possible that some journals will only provide the right to access and read manuscripts in the editorial management system, but not to send emails. If this is the case, the corresponding Editor (or designated person within the journal) will be informed to send the emails.

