#### 4.7 Randomisation and blinding

Articles, which meet the eligibility criteria as a primary report of an RCT, for which the journal decides to send out for external peer review will be randomised into one of the two groups (allocation 1:1). The randomisation list will be created by the study-randomizer system (43) using random block sizes between 2 and 8 and stratification by journal. As soon as the first peer-reviewer accepts the invitation, the manuscript will be included and randomised to one of the two intervention arms. One of the investigators (BS) will log onto the study randomizer-system (43) entering the study identification number (ID; provided from the Journal), the study title, as well as the journal the study was submitted to. Subsequently, all additional peer-reviewers accepting the invitation to review the same manuscript will receive the same intervention (C-short plus usual practice or usual practice only) as the first peer-reviewer.

Authors will be blinded to the intervention allocation. Editors will not be actively informed about the randomisation (possible exception listed under “4.3 Interventions”). To avoid potential bias, peer reviewers and manuscript authors will not be informed of the study hypothesis, design and intervention.

Outcomes will be assessed in duplicate (see assessment of outcomes). At least one outcome assessors will be blinded. Due to restricted resources it might be possible that the investigator conducting the randomisation (BS) will be included in the data-extraction from published manuscripts.

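### The sample C-short email does not name the manuscript it concerns, so a reviewer who also handles a control trial from the same journal could apply the checklist there

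*Protocol*

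**What the plan says.** **Unit of randomisation.** Sections 4.1 and 4.7 (Randomisation and blinding) of the protocol randomise individual articles 1:1, "using random block sizes between 2 and 8 and stratification by journal". Both arms therefore run side by side inside each journal.

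**Trigger for the email.** Section 4.3 ties the intervention to a particular article: "peer-reviewers who received a manuscript which was randomised to C-short will receive an additional email". The message is separate from the journal's standard mail: "This second email, containing the C-short checklist, is not generated automatically within the existing journal editorial management system". It follows a periodic check: "At least twice a week the editorial management system will be checked for each journal".

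**Text of the email.** Appendix 1 begins "We thank you for accepting to peer-review a manuscript for", then the journal's name. The reason follows: "As we are trying to improve the reporting for randomised controlled trials according to the CONSORT guidelines". The reviewer is asked to check ten items, and the message closes in the name of the journal's team. The only fields to fill in are the reviewer's title and name and the journal name. The text is presented as an example: "The exact wording might be slightly adapted according to the journal preferences".

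**Contamination.** Section 4.1 states that "the possibility that peer reviewer are invited to assess several RCTs and are randomised into both arms was judged as relatively small". It gives no figure, and the protocol describes no step to limit or record such overlap.

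**The concern.** The intervention belongs to one manuscript, but nothing in the sample text tells the reviewer which one. Section 4.7 keeps reviewers unaware of the hypothesis, design and intervention, so no other message tells them to confine the list to one paper. Two situations matter:

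- A reviewer holds two trial manuscripts for the same journal, one in each arm. The email does not say which it concerns, and because it is a separate message it need not arrive together with the acceptance.
- A reviewer receives a control trial from that journal later. The email has already presented better trial reporting as the journal's own aim.

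In either case the checklist may be used on a control manuscript. The control mean would then move towards the intervention mean, the estimated difference would shrink, and power would fall. A null result would be harder to read, because it could partly reflect control reviewers working from C-short.

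**Working it through.** **Step 1: the template against the design.** Section 4.3 sends the email because of one article's allocation. Appendix 1 has no field that carries that article's identity and no words that limit the request to it. The information exists: under section 4.7 (Randomisation and blinding) the investigator enters the journal's ID for the manuscript and its title when randomising.

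**Step 2: the plan's own sample sizes.** Inputs from section 4.6: SD 0.25, two-sided 5% t-test. Scenario 1 is 56% against 70% (difference 0.14) with 90% power. Scenario 2 is 71% against 82% (difference 0.11) with 80% power.

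Normal approximation: n per arm = 2 × (z₁ + z₂)² × SD² / difference².

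- Scenario 1: 2 × (1.960 + 1.282)² × 0.0625 / 0.0196 = 67.0, rounded up to 68. The t-test solution is 67.99, also 68. The protocol states 68.
- Scenario 2: 2 × (1.960 + 0.842)² × 0.0625 / 0.0121 = 81.1, rounded up to 82. The t-test solution is 82.05, so 83. The protocol states 83.

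Both figures reproduce. At 83 per arm the t-test power is 80.5% in scenario 2, so that scenario has almost no reserve. With the scenario 1 difference, 83 per arm gives 94.8%.

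**Step 3: illustration of leakage.** Let c be the share of the C-short effect that reaches the control arm, averaged over all control manuscripts, including those with no shared reviewer. The documents give no value, so c is an assumption. The remaining difference is planned difference × (1 − c). Power is from the two-sample t-test with 83 per arm and noncentrality (difference / 0.25) × √(83/2).

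| Assumed c | Scenario 2 difference | Power | n per arm for 80% | Scenario 1 difference | Power |
|---|---|---|---|---|---|
| 0 | 0.1100 | 80.5% | 83 | 0.1400 | 94.8% |
| 2% | 0.1078 | 78.9% | 86 | 0.1372 | 94.0% |
| 5% | 0.1045 | 76.3% | 91 | 0.1330 | 92.6% |
| 10% | 0.0990 | 71.8% | 102 | 0.1260 | 89.8% |

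**Step 4: what a given c would require.** Write c as the share of control manuscripts with a reviewer who has received the email, times the share of the effect carried over to them. If half the effect carries over (again an assumption), c = 5% needs 10% of control manuscripts to be affected (0.10 × 0.5), and c = 10% needs 20% (0.20 × 0.5).

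**Step 5: what c covers.** It is leakage from every cause. A reviewer who remembers the ten items contributes to it however the email is worded. The documents give no basis for separating the part due to the wording.

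**The case against.** The case against has real force.

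- **The text is a sample.** Journals may adapt it, and only the body is shown, without a subject line. A reader might infer that the emails actually sent will never name the manuscript; the protocol does not establish that. Equally, it does not require any version to carry an identifier.
- **The request is not addressed to all trials.** A reader might take the email as an instruction to use the list on every trial for that journal. It does not say so. The general phrase gives the reason, the opening speaks of one manuscript, and the message follows acceptance of one. A reviewer holding a single manuscript, probably the usual case, has little room for doubt.
- **The delay should not be exaggerated.** The check is made at least twice a week, so that frequency is a minimum.
- **The risk is acknowledged.** Section 4.1 names reviewer overlap and judges it small, and nothing in the documents contradicts that judgement. Misdirected use needs one reviewer, one journal and opposite arms.
- **Loss in the intervention arm is unlikely to be complete.** Every reviewer of a C-short manuscript is to receive the email, so all of them would have to attach it to another paper before that manuscript went without the list.
- **Scenario 2 is the demanding case.** The larger effect in scenario 1 leaves ample power.

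These points limit the likely size of the problem. They do not remove the gap between an intervention assigned to one manuscript and a sample text that fails to name it.

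**Conclusion.** The point holds as a minor weakness in the delivery of the intervention. The sample email does not identify its manuscript and rests its request on a general journal aim, in a design where both arms run within each journal and reviewer overlap is acknowledged. Any resulting use on control manuscripts would bias the primary difference towards zero.

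The size is unknown. A reader might infer from the table that the wording costs the trial up to about 9 percentage points of power (80.5% − 71.8% = 8.7). The documents do not support that: the leakage values are assumed, they cover all causes including recall, and the share due to the wording could be close to nil. The conclusion rests on the template and the unit of randomisation, and no loss of power has been shown. The sample size calculation itself is correct on its stated inputs.

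**What to change.** In Appendix 1:

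1. Put the manuscript ID and title in the subject line and in the first sentence.
2. Limit the request to that article, for example: *for this manuscript, please check whether the following items are adequately reported*.
3. State that every journal-adapted version, including emails sent by journal staff, must keep both elements.

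The cost is a merge field and a few words. The ID and title are already entered at randomisation, the change tells reviewers nothing about the trial, and the analysis and sample size are unaffected. It has to be in place before emails go out, because it cannot be applied to those already sent. It reduces misdirected use but leaves carry-over from what reviewers remember. Recording which reviewers appear in both arms would allow the judgement in section 4.1 to be checked afterwards.

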| 6    | Outcomes and estimation (17a/b) | For the primary outcome, results for each group, and the estimated effect size and its precision (such as 95% confidence intervals)                                                     | Is the estimated effect size and its precision (such as standard deviation or 95% confidence intervals) for each treatment arm reported? When the primary outcome is binary, both the relative effect (risk ratio, relative risk) or odds ratio) and the absolute effect (risk difference) should be reported with confidence intervals. |
| 7    | Harms (19)                      | All-important harms or unintended effects in each group                                                                                                                                 | Is the number of affected persons in each group, the severity grade (if relevant) and the absolute risk (e.g. frequency of incidence) reported? Are the number of serious, life threatening events and deaths reported? If no adverse event occurred this should be clearly stated.                                                      |
| 8    | Registration (23)               | Registration number and name of trial registry                                                                                                                                          | Is the registry and the registration number reported? If the trial was not registered, it should be explained why.                                                                                                                                                                                                                       |
| 9    | Protocol (24)                   | Where trial protocol can be accessed                                                                                                                                                    | Is it stated where the trial protocol can be assessed (e.g. published, supplementary file, repository, directly from author, confidential and therefore not available)?                                                                                                                                                                  |

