| Item           | CONSORT item                  | Scenario 1. Adequate reporting as published in WebCONSORT | Scenario 2. Adapted from Scenario 1 |
|----------------|-------------------------------|-----------------------------------------------------------|-------------------------------------|
| 1              | Outcomes (6a)                 | 77% (79 of 103)                                           | 77% (79 of 103)                     |
| 2              | Sample size (7a)              | 83% (85 of 103)                                           | 83% (85 of 103)                     |
| 3              | Sequence generation (8a)      | 76% (78 of 103)                                           | 76% (78 of 103)                     |
| 4              | Allocation concealment (9)    | 55% (57 of 103)                                           | 55% (57 of 103)                     |
| 5              | Blinding (11a)                | 35% (36 of 103)                                           | 35% (36 of 103)                     |
| 6              | Outcomes and estimation (17a) | 44% (45 of 103)                                           | 44% (45 of 103)                     |
| 7              | Harms (19)                    | 71% (73 of 103)                                           | 71% (73 of 103)                     |
| 8              | Registration (23)             | 69% (71 of 103)                                           | 90%                                 |
| 9              | Protocol (24)                 | 19% (20 of 103)                                           | 90%                                 |
| 10             | Funding (25)                  | 34% (35 of 103)                                           | 90%                                 |
| Overall |                               | 56%                                                | 71%                          |

Abbreviation: CONSORT= CONSolidated Standards for Reporting Trials

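### The example C-short email leaves out the request to authors that section 4.3 makes part of the intervention, and the item 6 explanation conflicts with its own CONSORT text

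*Protocol*

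**What the plan says.** **The intervention.** Protocol section 4.3 (experimental group) says that reviewers will be asked to attend closely to the C-short items and to "request authors to report on these items, if not already adequately reported". The control group receives the journal's usual email and no second email.

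**The email.** Appendix 1 gives the example of the C-short email. Its request reads "we would like to ask if you could check whether the following most important and poorly reported items are adequately implemented". The ten-item table follows, and the email ends with "Your efforts are highly appreciated".

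**Freedom to change the wording.** Section 4.3 says "the exact wording might be changed according to the preferences of the participating journals"; Appendix 1 says "The exact wording might be slightly adapted according to the journal preferences".

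**Item 6.** In Table 1 and again in Appendix 1, the CONSORT column asks, for the primary outcome, for "results for each group, and the estimated effect size and its precision (such as 95% confidence intervals"). The short explanation in the same row asks: "Is the estimated effect size and its precision (such as standard deviation or 95% confidence intervals) for each treatment arm reported"? A further sentence of the explanation requires relative and absolute effects with confidence intervals when the primary outcome is binary. Both places label the item 17a/b. Table 3 in section 4.6 labels it "Outcomes and estimation (17a"), without the b.

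**Scoring.** Section 4.4 (data collection methods) scores published articles against the C-short checklist. It lists sub-items for items 6a, 7a, 11a and 25, and none for item 6 of the short list.

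**The concern.** The second email is the only thing that separates the arms, and the primary outcome is read from the published article. An effect therefore has to pass from reviewer to author to revised text. Section 4.3 asks reviewers explicitly to take the reviewer-to-author step; the drafted email does not. If it goes out as drafted, what is delivered and what is described differ in the component closest to the outcome, and a reader of the results could not tell which of the two had been tested.

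The item 6 row contains two standards. An effect size is a contrast between arms, so it cannot be reported for each arm. A standard deviation describes the spread of observations, not the precision of an effect estimate. Because the same checklist serves reviewers and assessors, the conflict can affect both what reviewers ask for and how articles are scored.

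**Working it through.** **1. Email against section 4.3**

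| Element | Section 4.3 | Appendix 1 |
|---|---|---|
| Attend to or check the ten items | Yes | Yes |
| Ask authors to report what is missing | Yes | No such sentence before or after the table |
| Wording may be adapted to journal preference | Yes | Yes, slightly |
| Minimum content that must stay | None stated | None stated |

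Nothing says that the missing request will be added when the email is adapted.

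**2. Item 6: CONSORT column against explanation**

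Take an article that reports mean (SD) in each arm for a continuous primary outcome and gives no between-group difference or confidence interval.

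- By the CONSORT column: results per group are present, but the effect estimate with its precision is absent. Not adequate.
- By the first sentence of the explanation, read literally: a figure per arm with a standard deviation is present. Adequate.

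If the primary outcome is binary, the next sentence of the explanation asks for relative and absolute effects with intervals, so per-arm figures alone fail on either reading. The conflict is therefore mainly one for non-binary outcomes. With no sub-items listed for item 6, the rule that all relevant sub-items must be adequate does not settle it.

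**3. The plan's own figures reproduce**

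Inputs from section 4.6: Scenario 2, 71% against 82%, SD 0.25, two-sided 5%, power 80%; Scenario 1, 56% against 70%, SD 0.25, power 90%.

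- Scenario 2: difference 0.82 − 0.71 = 0.11. Normal approximation: n = 2 × (1.960 + 0.842)² × 0.25² / 0.11² = 81.1, so 82 per arm. The t-test gives 82.05, so 83 per arm and 166 in total, as stated. Power at 83 per arm is 80.5%.
- Scenario 1: difference 0.14. The t-test gives 67.99, so 68 per arm and 136 in total, as stated.
- Table 3, Scenario 1: the ten counts sum to 579, and 579 / 1030 = 56.2%. Scenario 2: (453/103 + 3 × 0.90) / 10 = 71.0%. Both agree with the table.

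**4. Weight of item 6**

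Item 6 is 1/10 of the score. The rounded Scenario 2 rates sum to 711, a mean of 71.1%. Replace the 44% for item 6 by *assumed* rates for strict and lenient scoring:

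- 20%: (711 − 44 + 20) / 10 = 68.7%
- 80%: (711 − 44 + 80) / 10 = 74.7%

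This moves the level, under one rule for both arms. The sample size uses only the difference (0.11) and the SD (0.25), so 166 stands.

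**5. What a weaker email could cost (illustration only)**

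The documents give no dilution figure. Under *assumed* reductions of the 0.11 difference, with 83 per arm and the t-test:

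| Reduction | Difference | Power |
|---|---|---|
| none | 0.110 | 80.5% |
| 10% | 0.099 | 71.8% |
| 20% | 0.088 | 61.6% |
| 30% | 0.077 | 50.5% |
| 50% | 0.055 | 29.1% |

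The table shows how sensitive power is to dilution. It does not estimate the dilution.

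**The case against.** **On the email.** Appendix 1 is an example that journals may adapt, section 4.3 states the fuller requirement, and the final emails are not shown. Section 2 frames the hypothesis as reminding reviewers of the items, and section 3.1 as asking them to use the short checklist; the drafted email does both. Its recipients have just agreed to write a review, and raising shortcomings is what a review ordinarily does. All of this stands. A reader might infer that every email will lack the request, or that a null result would be no test of the trial's hypothesis. The documents support neither. What remains is that the only email text given is narrower than the only operational definition given, and that nothing protects the missing component.

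**On item 6.** The correct requirement is printed beside the faulty explanation, and binary outcomes are covered. Scoring is by two independent assessors with expertise in trial reporting, with consensus or a third assessor and a piloted extraction form. That also stands. It would be too strong to say that item 6 itself is wrongly defined or that reviewers will pass deficient articles: the item is right, its explanation is not, and the extraction form is not shown. Piloting can harmonise assessors but does not correct what reviewers receive.

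**On the label.** A reader might infer that the 44% in Table 3 covers 17a alone. It may equally be a labelling slip; the documents do not say.

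**Conclusion.** Two wording faults hold and are worth correcting.

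- The example email omits the request to authors that section 4.3 includes. If sent as drafted, it delivers less than the intervention described, by an amount that cannot be derived from the documents.
- The item 6 explanation conflicts with the CONSORT text in its own row. For non-binary primary outcomes, someone relying on the explanation could accept mean (SD) per arm without a between-group estimate and confidence interval.

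The second fault touches one item of ten. The scoring rule is common to both arms, so leniency or strictness does not in itself bias the comparison. No stated figure is wrong and the sample size of 166 is not affected. The scoring range and the power losses shown above rest on assumed values.

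**What to change.** 1. Add a sentence to Appendix 1, for example: *If any item is not adequately reported, please ask the authors in your report to add it.* State in section 4.3 that this sentence stays when a journal adapts the email.
2. Reword the item 6 explanation in Table 1 and Appendix 1, for example: *Are results reported for each group, together with the estimated between-group effect and its 95% confidence interval? For a binary primary outcome, are both the relative and the absolute effect given with confidence intervals?* Use this wording for scoring under section 4.4.
3. Align the item label: 17a/b in Table 1 and the email, 17a in Table 3.

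The cost is minor text edits before launch. Journals must be shown the revised email. Wording already sent to reviewers cannot be corrected afterwards.
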